#### Secondary outcomes measurement

Differences between both groups with respect to the following:
***Sociodemographic outcomes:*** mother’s age, schooling level (without any studies, primary, secondary, University studies), marital status (single, married, divorced, widow), work status (self-employed, employed, unemployed), occupation, working hours/week, home country.***Breastfeeding outcomes:****Breastfeeding observation form (BREAST):* it is a tool developed by a WHO experts committee in 1992 [24], which collects the key points in order to assess a breastfeed through observation: body position (B), responses (R), emotional bonding (E), anatomy (A), suckling (S), and time spent suckling (T). In the Baby-Friendly Hospital Initiative (BFHI) strategy [27], it is specified that a complete breastfeed observation by an expert is essential for checking whether there is an appropriate transfer and for diagnosing the cause of possible difficulties, should there be any, for further resolution.*Breastfeeding Self-Efficacy:* a reduced version of the *Breastfeeding Self-Efficacy Scale-Short Form* (BSES-SF) [30] scale [26] which was validated in Spanish by Oliver-Roi et al. [26], and counts on 14 items grouped in only one dimension. It is a one-dimensional, self-completed scale of 14 items, positively presented and preceded by the sentence ‘I always can’. For scoring, it has a Likert-type scale from 1 to 5, where 1 indicates ‘not sure at all’ and 5 indicates ‘very sure’. Higher scores mean higher self-efficacy levels for breastfeeding. The BSES-SF Spanish version’s reliability, measured with the Cronbach alpha coefficient, is 0.92. It is a valid and reliable measure, successfully adapted into diverse cultural contexts, including the Spanish [26, 31].*Previous breastfeeding experiences*: multiparous women will be asked about their experience with breastfeeding while raising previous children, as well as the reason for giving it up.*Type of infant feeding after hospital discharge*: exclusive breastfeeding, nearly exclusive breastfeeding, partial breastfeeding, formula feeding.*Common breastfeeding problems and solutions* (consultation with the midwife, Internet, social networks, reference person …).*Reasons for breastfeeding interruption:* mother’s decision, low weight gain, mother’s disease, newborn’s disease, contraindication due to medication, nipple problems, difficulties with the technique, return to work, etc.***Obstetric outcomes:*** mode of birth (eutocic/dystocic/C-section), mode of start of labour (spontaneous/induced), analgesia during labour (epidural/others), perineal trauma classification (episiotomy/perineal tear degree), initiation of skin-to-skin contact immediately after birth.***Neonatal outcomes:****Perinatal aspects*: newborn’s gender (female/male), weight (expressed in grams), Apgar test score [32], admission in neonatal care unit (yes/no).*Newborn’s health problems in the first 6 months of life:* description for subsequent coding.***Behaviour outcomes:****General Self-Efficacy*: this scale assesses optimistic self-beliefs of coping efficiently with a variety of difficult demands in life. Baessler and Schwarzer’s adaptation [33] will be used, although, in spite of its original format, a ten point Likert-type answer scale suggested by Sanjuan et al. [25] will be used, consisting of 10 items and a scoring range from 10 to 100, with an internal consistency of 0.87 (Alpha coefficient) and a correlation between two halves of 0.88.***Outcomes related to the use of social networks for support:*** frequency of use of social networks and/or WhatsApp, number of times the resource is used, questions resolved through face-to-face appointment in the midwife clinic, use of the App for consultation regarding breastfeeding.

Table 1 shows the measurement tools used for data collection, the method of collection and time points.

**Table 1 Tab1:** Measurement domains, survey tools, and collection time point

Variable	Component	Measurement tools/ Questions	Baseline	2mth	4mth	6mth
*Sociodemographic measures*		Age, schooling level, marital status, employment, ethnicity.	✓			
*Clinical information*	Obstetric outcomes	Type of birth, onset of labour, type of analgesia, perineal trauma, skin-to-skin technique	✓			
	Neonatal outcomes	Gender, weight, Apgar, neonatology admission, health problem	✓			
*Breastfeeding measures*	Previous experience	In affirmative case, interruption motivation	✓			
	Type of breastfeeding	Exclusive breastfeeding, nearly exclusive breastfeeding, partial breastfeeding, formula	✓	✓	✓	✓
	Breastfeeding information	Breastfeeding observation form (BREAST)	✓			
	Breastfeeding Self-Efficacy	Breastfeeding Self-Efficacy Scale-Short Form (BSES-SF)	✓	✓	✓	✓
	Breastfeeding problems	Type of problem and resolution (midwife, peer, social network, Internet …)	✓	✓	✓	✓
	Breastfeeding Interruption - Motivation			✓	✓	✓
*Behaviour measures*	Self-Efficacy General Scale		✓	✓	✓	✓
*Social networks (intervention group)*	Use and frequency			✓	✓	✓
	Problem consulted			✓	✓	✓
*Clinical services*	Appointments related to breastfeeding attended			✓	✓	✓

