A follow-up at the first two, four, and six months after birth will be performed; at these points, the main outcome variables will be collected (current way of feeding, dropout register, obstacles, ICTs use register, neonatal admission, return to work) and the same scales as in the first visit, previously mentioned, will be once again administered.

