#### Control group

The women in the control group will receive the usual antenatal care according to the pregnancy, birth, and postpartum care protocol of the Department of Equality, Health and Social Policies of the Regional Government of Andalusia [29], regarding antenatal and postnatal care, as well as the women in the intervention group.

Besides, they will have the option of asking for individual on-demand appointments with their reference midwife at the health centre they belong to.

The first postpartum visit will take place before the first ten days and the follow-up will be performed after the first two, four, and six months after birth; at these points, the main outcome variables will be collected (current way of feeding, dropout register, obstacles, ICTs use register, neonatal admission, return to work) and the same scales as in the first visit, previously mentioned in the intervention group, will be once again administered [24–26].

Figure 1 details the flow of participants from recruitment until the last follow-up contact for control and intervention subjects.

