## Discussion

There is no breastfeeding follow-up nor tracking system in Spain. Data come from studies conducted by health professionals at the regional level and they do not allow for a correct assessment nor for following up in time. Spanish statistics suggest that the breastfeeding time average is 3–5 months, the biggest amount of withdrawals happening over the first 4 weeks, and the second biggest one between the third and the fourth month, due to the mother’s return to work [38].

Taking these limitations into account, and according to the data collected from the Spanish National Health Survey (*Encuesta Nacional de Salud*), the breastfeeding rate in Spain (including partial breastfeeding and EB) at the first 6 weeks has been kept mostly stable, with global numbers around 71%, while in the last 15 years it has been possible to observe a progressive increase of breastfeeding at 3 (66.5% in the year 2012) and 6 months of life (46.9%). On the other hand, the EB percentage at 6 months in 2012 was over 28.5%, a percentage similar to the European global numbers but far from the WHO-UNICEF recommendations [39].

International studies have proved that 54% of newborns had received formula milk at some time in their first week of life, and the vast majority of them, in their first year of life [40]. This brings to light how usual it is to complement breastfeeding with formula milk. In this sense, the improvement of the professionals’ training on breastfeeding and the promotion of family and social support for breastfeeding mothers are two key points in order to increase the prevalence of EB [41].

There already are breastfeeding support groups led by midwives in Spain nowadays [42], but they do not follow a common structure or systematization that allows for impact assessment. This project aims to develop a common structure based on prenatal counselling, antenatal classes and a follow-up over the first 6 months of the newborn’s life, by means of monthly group sessions and mother-to-mother support through social networks (Facebook and WhatsApp), a support resource described in the previous literature [28], and to assess their efficacy. This will help elaborate a guide which can offer a direction to those professionals who wish to set up a breastfeeding support group in their primary health centre.

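### Newborn health problems are a 6-month between-group outcome, but Table 1 schedules them at baseline only and neither follow-up list names them

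*Protocol article*

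**What the plan says.** Under Secondary outcomes measurement, the list introduced as differences between the two groups includes, among the neonatal outcomes, the newborn's "health problems in the first 6 months of life", recorded as a description to be coded later. The same list places "admission in neonatal care unit (yes/no" under perinatal aspects, next to sex, weight and Apgar score.

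The article gives Table 1 a scheduling role: "Table 1 shows the measurement tools used for data collection, the method of collection and time points". Its neonatal row reads "Gender, weight, Apgar, neonatology admission, health problem". That row has one tick, under Baseline, and its 2, 4 and 6 month cells are empty.

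The Intervention group section states "A follow-up at the first two, four, and six months after birth will be performed", and the Control group section states "the follow-up will be performed after the first two, four, and six months after birth". Both give the same list of main outcome variables for those contacts: "current way of feeding, dropout register, obstacles, ICTs use register, neonatal admission, return to work". The self-efficacy and observation scales are repeated as well. Newborn health problems are not in the list.

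In both arms the first postpartum visit, which serves as baseline, falls within about ten days of birth.

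**The concern.** An outcome defined over six months has to be asked about during those six months. Here the outcome definition says six months, the schedule says baseline, and the follow-up procedures are silent. Follow-up data come from the App or from online questionnaires that the women complete (Data collection), so an item that is not built into those forms is not asked.

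At stake is a secondary comparison. If health problems are recorded only at about ten days, illness that begins later is absent from both arms and the planned comparison says nothing about it. The Adverse events section foresees none, so it offers no other systematic route to later infant health.

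Two neighbouring items raise a lesser question. Neonatal admission and return to work are in the follow-up lists, but Table 1 ticks the first at baseline only and has no row for the second. Return to work matters to the study's own reasoning: the Discussion gives it as the cause of one wave of stopping, "the second biggest one between the third and the fourth month".

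**Working it through.** The plan states no figure to reproduce. The check is a comparison of places, followed by one ratio.

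**Step 1: the places side by side**

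| Item | Secondary outcomes measurement | Table 1 | Follow-up lists, both arms |
|---|---|---|---|
| Newborn health problems | first 6 months, compared between groups | baseline only | not named |
| Neonatal admission | perinatal aspect, yes/no | baseline only | 2, 4 and 6 months |
| Return to work | only as one reason for interruption | no row (employment at baseline only) | 2, 4 and 6 months |
| Type of feeding (primary outcome) | outside this list; Primary outcomes measurement gives ten days, 2, 4 and 6 months | baseline, 2, 4 and 6 months | 2, 4 and 6 months |

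**Step 2: is the single tick an extraction fault?** Unlikely. Other rows of the same table, such as type of breastfeeding and breastfeeding problems, carry their ticks at 2, 4 and 6 months.

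**Step 3: how much of the window is scheduled for newborn health problems?** The baseline visit is at most about day 10. Six months is taken as about 182 days.

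- Covered: 10/182 = 0.055, about 5%.
- Not covered: (182 − 10)/182 = 172/182 = 0.945, about 95%.

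This ratio applies to health problems only. The follow-up lists name the other two items at 2, 4 and 6 months.

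**Step 4: does another row stand in for the missing ones?** Interruption motivation is ticked at 2, 4 and 6 months, and the reasons listed for it include newborn disease and return to work. It records either one only when it is the reason for stopping. It misses an infant who is ill while breastfeeding continues. It also misses a mother who returns to work and keeps breastfeeding, and she belongs to the comparison group needed to study return to work as a factor in sustainment.

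**The case against.** The best reply is that Table 1 is a summary in a condensed article and the questionnaires are not shown. Nothing says that the forms were built from the table, and the prose on follow-up is what staff would follow. For neonatal admission and return to work this largely succeeds, because both arms' lists collect them at 2, 4 and 6 months. For admission, Table 1 also agrees with the perinatal definition among the secondary outcomes, so the text itself is split and the table is not plainly the place in error. For newborn health problems the reply fails: the prose on follow-up does not name them either.

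A second reply is that later illness would surface by other routes: as an obstacle, as a reason for stopping, through the admission item, or from medical records of a hospital stay. This stands in part. Each route sees some cases, but none is a scheduled record of health problems in all infants, and the article does not say whether the record review reaches infant stays after baseline.

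A third reply is that this is a descriptive secondary item with no role in the sample size or the effectiveness analysis. That is correct and limits the weight of the point.

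A reader might also infer more than the article supports:

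- That return to work and later admissions will be lost. The follow-up lists say otherwise.
- That the objective on reasons for interruption is weakened. Return to work is one of the listed reasons, and that row is ticked at every follow-up.
- That this is the only infant-benefit or harm outcome. Neonatal admission at follow-up would be another.
- That baseline always precedes the first support session. The article gives no date for the first session.

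**Conclusion.** The contradiction over newborn health problems is in the current text. The outcome is defined over six months, its only scheduled collection is at baseline, and the follow-up lists omit it. Followed as written, about 5% of its window is covered and a later group difference cannot appear. This rests on baseline falling no later than about day 10, on six months being about 182 days, and on the forms following the article. If the questionnaires already ask about infant health at 2, 4 and 6 months, no data are lost and only the text needs correcting.

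The other two mismatches are real but smaller. Return to work lacks a row in Table 1 although the prose collects it, and the timing of neonatal admission differs between the follow-up lists on one side and Table 1 with the outcome definition on the other. These are matters of reconciliation.

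Type of feeding is scheduled at all four time points, so the primary outcome, the sample size and the effectiveness analysis are untouched. The correction should still be made before the follow-up forms are fixed, because events not asked about at the time may be hard to recover.

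**What to change.** 1. In Table 1, take newborn health problems out of the baseline-only neonatal row and give them their own row, ticked at baseline, 2, 4 and 6 months, for all women in both arms whatever the feeding status. Sex, weight and Apgar score stay at baseline.
2. Add newborn health problems to the follow-up lists in the Intervention group and Control group sections.
3. Add a return-to-work row to Table 1, ticked at 2, 4 and 6 months, so that it agrees with those lists.
4. State one timing for neonatal admission and make Table 1, the perinatal definition and the follow-up lists agree. This does not call for widening the variable to any hospital admission, which the article does not define.

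Cost: one extra item in questionnaires already sent at 2, 4 and 6 months, plus corrections to the table and text. Return to work adds no new collection, since the prose already requires it.

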### Process evaluation

The follow-up will be conducted by a qualified researcher, independent from the study group, without any conflict of interest. They will verify the notification of participation in the study and the appropriate tracking of participants by the researchers.

During the whole study process, a continuous follow-up will be performed, which will allow for the identification of potential problems and solutions, implementing the required changes in a short term. This study will count on an expert researcher, responsible for monitoring the participant centres, as well as the participants’ compliance with the follow-up protocols. A global report about the study status will be elaborated biweekly with the lead researcher. The midwives recruiting patients in the health centres will be contacted monthly, in order to let them know the number of women recruited, as well as the follow-up situation performed. All the study data will be included in an electronic database by the research team. All information will be pre-coded and kept safe in a database. During the research, the lead researcher, along with the expert, will have access to that database.

### Withdrawal

Any participant can withdraw from the study at any moment and by any given reasons, either because she repeatedly breaks the follow-up protocol or, if she is allocated to the intervention group, because she does not want to keep on attending the breastfeeding support group sessions any longer. Anyway, the withdrawal reason will be kept for the record for further study. The participants who withdraw from the study will not be replaced.

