#### Data collection

Once the woman is randomized to the control or intervention group and has signed the written consent, having been previously informed of the study objectives, the midwife will let her know about the follow-up she will need to perform throughout the study. The woman will have to choose whether she prefers to be followed up via the GALMA Project application (App), or by filling in online questionnaires via WhatsApp®.

The previously mentioned basal follow-up will be conducted and the participants will have to facilitate the information using the study App, which will have previously sent a reminder message to them. Those women who opt to fill in online questionnaires will receive a phone call the previous day from a member of the research team, who will send to them the link to the questionnaires. Data related to the monitoring, both electronic and via the App, will be coded and saved by the research team. Those data related to obstetrical results and those derived from a hospital stay will be drawn from the patient’s medical record, after the patient’s consent.

Incorrect or missing data will be checked by the members of the research team and the participants will be asked for their fulfilment. All data will be recorded in an electronic database with access only by the team members. Hard copies of the participants’ questionnaires will be kept in a safe and secure file which can be accessed only with previous authorization.

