### Study sample size

Taking into account that the EB rate in Andalusia is 25%, this is considered the expected value in the control group. An estimated increase effect of 12% of the EB rates at 6 months is established, as asserted in previous studies [34]. To reach this difference between both groups, a two-tail hypothesis is set out, with a power of 80% and assuming a type I error of 5%, assuming a loss of 10% in the follow-up, the necessary sample increases to 512 women, 256 in each group. Missing values in the follow-up will be addressed by multiple imputation technique, performing attrition analysis.

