### Analysis

A complete statistical analysis plan will be previously performed, as well as a report thereof and of the results, according to the Consolidated Standards of Reporting Trials (CONSORT) [35, 36]. The analysis will be carried out on the basis of an intention-to-treat principle, without taking into account whether or not adherence to the breastfeeding support group was completed. Individual health centres are the randomization units and the mother-newborn dyad will be the analysis unit. All statistical trials and confidence intervals will be assumed with a type I error established in alpha = 0.05, using the IBM SPSS V22 statistics package [37].

An exploratory data analysis will be conducted in order to identify atypical values, for the total of our studied sample, as well as for the different sub-groups created. A graphic exploratory analysis of the different studied variables will also be conducted, according to their numerical or non-numerical character. Frequency and percentage distribution scales will be elaborated for the descriptive analysis of variables with a qualitative (non-numerical) character. For the quantitative (numerical) ones, centralization and dispersion measures will be calculated. In variables with a normal distribution, the mean and the standard deviation will be calculated and, in those with an asymmetric distribution, the mean and interquartile range (p25-p75) will be calculated. Furthermore, point estimators and confidence intervals will be calculated at 95% for averages and percentages. The relationship between two qualitative variables will be analysed with Pearson’s chi-square test, the correction for continuity of the chi-square test, a linear-by-linear association test, and Fisher’s exact probability test, based on the application criteria. The significant results of these tests will be complemented with a confidence interval set at 95% for percentage differences.

Regarding the numerical variables between two groups, the Student’s t-test of independent samples for mean comparisons will be carried out, once the requirements of randomness, normality (Kolmogorov-Smirnov’s test, or Shapiro-Wilks’ test, according to the sample size) and equality of variances (Levene’s test) are validated. In case this one is not achieved, the Student’s t-test for independent samples with Welch’s correction will be carried out. In case normality requirements are not accomplished, the Mann-Whitney’s U test will be applied.

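### The withdrawal rule does not separate stopping the support-group sessions from leaving outcome follow-up, which opens an exit route in the intervention arm only and works against the intention-to-treat rule

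*Protocol article*

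**What the plan says.** All references are to the protocol article.

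- **Withdrawal.** The rule is permissive and general: "Any participant can withdraw from the study at any moment and by any given reasons". Two reasons are then named. One can arise in either arm: "either because she repeatedly breaks the follow-up protocol". The other belongs to one arm: "if she is allocated to the intervention group, because she does not want to keep on attending the breastfeeding support group sessions any longer". The reason for leaving is recorded, and "The participants who withdraw from the study will not be replaced". The section does not say whether feeding data are still sought from a woman who leaves on either ground.
- **Analysis.** The analysis follows intention to treat, "without taking into account whether or not adherence to the breastfeeding support group was completed".
- **Study sample size.** "Missing values in the follow-up will be addressed by multiple imputation technique, performing attrition analysis". The mechanism assumed and the variables in the imputation model are not given. A single 10% loss is assumed, not split by arm.
- **Data collection and follow-up.** Each woman chooses whether "she prefers to be followed up via the GALMA Project application (App), or by filling in online questionnaires via WhatsApp". For the intervention group, "A follow-up at the first two, four, and six months after birth will be performed", and the control group has the same time points. Obtaining the outcome therefore does not depend on attending sessions.
- **Primary outcomes measurement.** Exclusive breastfeeding (EB) means breast milk only, from birth to 6 months.

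**The concern.** Not wanting to attend sessions any more is a reason to stop the intervention. It is not in itself a reason to stop answering a feeding question at 2, 4 and 6 months. The Withdrawal section offers it as a reason for leaving the study, and nowhere says that outcomes are still collected.

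The intention-to-treat rule is most useful when the 6-month feeding of non-attenders is observed. A recruiting midwife who follows the Withdrawal section literally could close follow-up for those same women. Only the intervention arm has sessions to stop, so this route has no counterpart among controls.

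The loss is also unlikely to be neutral, because a woman who has stopped breastfeeding has less reason to come to a breastfeeding group. If such women go unobserved, the EB rate among the intervention women who remain is too high and the effect estimate is biased towards benefit. The trial is unblinded, so nothing in the design masks or balances this.

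**Working it through.** **1. The passages side by side.** The Analysis section needs outcomes irrespective of attendance. The Data collection section provides a route to them irrespective of attendance. The Withdrawal section makes non-attendance a named ground for leaving the study. The first two fit together; the third works against them.

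**2. The plan's own sample size.** Inputs from Study sample size: 25% v 37% (12 points), two-sided 5%, power 80%, 10% loss.
- Unpooled: (1.960 + 0.842)² × (0.25×0.75 + 0.37×0.63) / 0.12² = 229.3, so 230 per arm; 230/0.9 = 255.6, so 256 per arm and 512 in total.
- Pooled: 232 per arm; 232 × 1.10 = 255.2, so 256 per arm; or 232/0.9 = 257.8, so 258 per arm.

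The stated 512 is reproduced. It contains the common 10% loss and nothing extra for an intervention-only route.

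**3. Size of a possible bias (illustration).** The documents give neither the share leaving by this route nor the leavers' EB rate, so both are assumed. Let w be the share of otherwise observed intervention women who leave, q their true EB rate, and 25% the true rate in both arms (no effect). With no control-arm loss, the rate among retained intervention women is

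(0.25 − w×q) / (1 − w).

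| w | q | Retained rate | Spurious difference |
|---|---|---|---|
| 10% | 10% | 0.240/0.90 = 26.7% | +1.7 points |
| 10% | 5% | 0.245/0.90 = 27.2% | +2.2 points |
| 20% | 10% | 0.230/0.80 = 28.75% | +3.75 points |
| 20% | 5% | 0.240/0.80 = 30.0% | +5.0 points |
| any | 25% | 25.0% | 0 |

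The extremes are wider. With q = 0 the difference is 0.25/0.90 − 0.25 = +2.8 points at w = 10%, and 0.25/0.70 − 0.25 = +10.7 points at w = 30%.

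Control-arm loss of the same kind offsets this. If controls lose 10% at q = 5% while the intervention arm loses 20% at q = 5%, the difference is 30.0 − 27.2 = +2.8 points. Equal loss in both arms gives zero.

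**4. Power.** Suppose extra intervention loss of 10%, 20% or 30% of the 256, on top of 10% in each arm. Treating women as independent, power for 25% v 37% falls from 79.7% to 77.4%, 74.5% or 70.9%. Up to about 20% extra loss this is modest; bias is the larger risk.

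**5. What imputation can reach.** Table 1 records feeding type and breastfeeding self-efficacy at baseline, 2, 4 and 6 months. A woman who leaves after the 2- or 4-month record has informative data, and a model using them could remove much of the bias. A woman who leaves before 2 months has only her baseline record, when inclusion required exclusive or partial breastfeeding. An imputation that assumes missing at random would give her roughly the rate of similar retained women in her arm, so the complete-case figures above are then a fair guide. The Discussion places the largest share of breastfeeding cessation in the first 4 weeks, so early leavers are not a remote case. If withdrawn women were censored at withdrawal in the Kaplan-Meier, log-rank and Cox analyses, those would face the same difficulty.

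**The case against.** Three stronger readings are tempting, and the document supports none of them.

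- *Non-attenders are removed from the study.* The text says a participant can withdraw and gives reasons; it does not say that the team removes a woman who stops attending. One who stops sessions but stays in the study is covered by the intention-to-treat rule. The wording about repeated breaches of follow-up does read more like exclusion than choice, but it applies to both arms.
- *The Withdrawal section flatly contradicts intention to treat.* The two can be reconciled, because multiple imputation can keep withdrawn women in the analysis set. Whether the imputation would be good enough is a separate question.
- *Outcome data are lost in one arm only.* Only one named reason is specific to an arm. Women in either arm may leave for any reason, and controls who stop breastfeeding may also stop answering, which would partly offset the bias.

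It is also fair to say that the protocol never states a missing-at-random assumption, that the figures above describe a complete-case analysis and not the planned one, and that staff already check for missing data and ask participants to complete them. A missing-data sensitivity analysis is normal content for the separate statistical analysis plan, and its absence here is no fault.

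All of this limits the claim. It does not answer the remaining point: the Withdrawal section states a rule, and that rule joins stopping the sessions to leaving the study without saying that outcome follow-up continues.

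**Conclusion.** The point holds in a limited form. The withdrawal rule does not distinguish stopping the intervention from leaving follow-up. It thereby works against the adherence-blind analysis and opens an exit route that exists in one arm and is plausibly related to outcome. The planned imputation may not fully repair the loss, chiefly for women who leave before 2 months.

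The size cannot be fixed from the document. With an assumed 10–20% of the intervention arm leaving at a true EB rate of 5–10%, no control-arm loss and no true effect, a complete-case comparison shows a spurious +1.7 to +5.0 points, which at the top is 5.0/12 = 42% of the target difference. It is zero if leavers have the same EB rate as stayers, and smaller if imputation uses the 2- and 4-month feeding data or if controls are lost in the same way. The loss is avoidable, so the rule should be changed, but the document does not show that the trial's result will be biased.

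**What to change.** 1. Reword the Withdrawal section so that stopping the sessions, or missing contacts, ends neither follow-up nor inclusion in the analysis. Only withdrawal of consent to data collection ends follow-up.
2. State that the 2-, 4- and 6-month feeding data continue to be sought from every woman through the App or WhatsApp route already in place.
3. Count a woman already recorded as formula-feeding as not exclusively breastfeeding at 6 months instead of imputing her. This follows from the protocol's own definition of EB.

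Reporting loss by arm and by reason, and a sensitivity analysis counting missing 6-month outcomes as not EB, would be useful but can be left to the statistical analysis plan. The latter would tend to push the comparison against whichever arm loses more women, so it is a bound and not a replacement for the main analysis.

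The cost is a wording change and a few more reminder messages to women who have stopped attending. The sample size is unaffected.
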